### SAEs and unblinding: care of patients with AEs

All AEs and other study outcomes in the randomization, treatment, and follow-up periods will have to be reported. In case of mild or moderate AEs, the administration of BNZ will be suspended temporarily according to the clinical researcher’s decision. Symptomatic treatment will be provided to the patient according to the treating physician.

It will be considered that a patient has finished the study when he or she has completed the treatment and follow-up phase (per-protocol principle). The study may be interrupted in case of voluntary decision of the patient at any time if an AE forces interruption of the treatment, if significant protocol violations occur, or if the treating physician deems it would benefit the patient (intention-to-treat principle).

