### Randomization and follow-up

Patients are randomly assigned to receive BNZ 150 mg/day for 60 days, 400 mg/day for 15 days, or the standard scheme of 300 mg/day for 60 days. Because this is a double-blind trial, investigators and all sponsor staff will not be aware of the treatment allocation and randomization list until the end of the trial. Double-blinding will be adopted for all trial arms. Patients will be randomized 1:1:1, and randomization will be done via a remote and interactive response system, according to a predefined list. To avoid bias, randomization will be centralized and concealed. The treatment groups will be allocated on day 1 on the basis of a balanced block randomization, taking into account the country. Each patient will be assigned an identification code that will correspond to the trial kit number allocated to the patient. The label will indicate the trial number and the number of the kit, but it will not indicate the treatment designation.

Scheduled follow-up visits will occur at 7, 15, 28, and 60 days and up to 4, 6, 8, and 12 months after initiation of treatment. More information is provided in Fig. 1.

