	Selection visit (from − 3 months to day 0)	Baseline visit (day 0)	Treatment visit (day 7 ± 2)	Treatment visit (day 15 ± 3)	Treatment visit (day 28 ± 4)	End of treatment visit (day 60 ± 7)	Side effect visit (not scheduled)	Follow-up visit (months 4, 6, and 8)	Final visit (month 12)
**Informed consent**	x								
**Demographic data**	x								
**Pathological background**	x								
**Toxic habits**	x								
**Chagas disease history**	x								
**Concomitant medication**	x	x	x	x	x	x	x	x	x
**Directed anamnesis**	x	x	x	x	x	x	x	x	x
**Physical examination**	x	x	x	x	x	x	x	x	x
**Pregnancy test**		x							
**Hematology**	x		x	x	x	x	x		
**Biochemistry**	x		x	x	x	x	x		
**HLA**	x								
**Chest x-ray**	x								
**EKG**	x								
**PK**				x		x	x		
**Serology**	x								x
**PCR**	x		x	x	x	x		x	x
**Other complementary tests**	x								
**Adverse events**		x	x	x	x	x	x		
**Randomization**	x								
**Study medication**		x	x	x	x	x			

*Abbreviations: EKG* Electrocardiogram, *HLA* Human leukocyte antigen, *PCR* Polymerase chain reaction, *PK* Pharmacokinetics

During this phase, any patient may consult spontaneously for the eventual occurrence of any AE. The decision to interrupt the treatment will be according to the discretion of the clinical researcher treating the patient, taking into account the severity, intensity, and extent of these AEs. In addition, the patient may decide unilaterally to suspend or not the medication at any time during the treatment period.
4.**Follow-up phase**

Once the patient has taken the last dose of treatment, which may be at the end of the therapeutic scheme (day 60), when a severe AE that obliges the patient to suspend the medication occurs, or when the patient unilaterally decides to suspend the medication, this phase will begin, and it will last up to 12 months after randomization. The visit schedule of this phase is presented in Table 3.

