In addition, the mechanisms underlying BNZ toxicity are still not well understood. The production of several metabolites in the enzymatic reduction of the drug, their accumulation, and their interactions with cellular constituents could be the main reasons for producing these AEs [32, 33]. Some AEs of the drug have a certain temporal pattern. For example, dermatological and digestive manifestations usually tend to occur around day 10 of treatment, while neurological events and arthritis appear after day 40 of treatment, probably because they are related to the cumulative total dose and not to the serum concentration [9]. Age and female sex have also been considered as classic risk factor for AEs. However, there remains an important lack of knowledge about the mechanisms of toxicity [9, 10].

According to the duration of the treatment, two approaches were considered. Taking into account the cure rates of patients with CD treated with shorter courses of BNZ (those who had to interrupt the treatment because of AEs), a shortened regimen has been incorporated. Finally, researchers explored the possibility of including a new arm with prolonged exposure. Unfortunately, due to the lack of clinical published experience and the potential risk of gonadal toxicity and its effect over the pituitary–testicular axis, that treatment arm was discarded [34, 35].

Another aspect that will be assessed is the genetic variability of the parasite over the treatment response. The great majority of randomized clinical trials have been conducted in Argentinean or Bolivian patients, and scarce information is available in other geographical regions. In any case, the few existing data suggest an important effect of parasitic diversity in the treatment efficacy and response [17, 36].

Therefore, this clinical trial will evaluate the efficacy and safety of different dosing regimens of BNZ compared with the standard treatment scheme. Experimental dosing regimens have been chosen on the basis of evidence derived from previous studies, in which it has been found that shorter-duration schemes and/or lower dose with the same duration could achieve the same cure rate. Moreover, higher doses could be used without entailing a higher rate of AEs. The results of this clinical trial will help to better identify the most adequate BNZ regimen in terms of efficacy and safety for the treatment of CD in the chronic phase.

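### Table 3 has no adverse-event mark at the month 4, 6, 8 and 12 visits, although the text requires adverse events in follow-up to be reported

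*Protocol article*

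**What the plan says.** The section SAEs and unblinding: care of patients with AEs sets a general rule: "All AEs and other study outcomes in the randomization, treatment, and follow-up periods will have to be reported".

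Under Study organization, the follow-up phase starts after the last dose and runs to 12 months from randomization. For its visits the reader is sent to Table 3. There the row "Adverse events" is marked at baseline, at days 7, 15, 28 and 60, and at the unscheduled side effect visit. It is blank in the column for months 4, 6 and 8 and in the month 12 column. The row "Directed anamnesis" is marked in all nine columns, as are physical examination and concomitant medication. Hematology and biochemistry are blank at months 4, 6, 8 and 12.

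The text on unscheduled contact belongs to the treatment phase: "During this phase, any patient may consult spontaneously for the eventual occurrence of any AE".

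On timing of toxicity, the Discussion says that "neurological events and arthritis appear after day 40 of treatment", and gives cumulative dose as the probable reason. Sample size and data analysis plans AE incidence rates with 95% confidence intervals per arm and does not name the observation period.

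**The concern.** Text and table cannot both be followed as written. The text makes AE reporting a duty until the end of follow-up. The table lists AEs as an item separate from history-taking and examination, keeps it through day 60, and then drops it while the other two continue. A site that works from the schedule could reasonably take this to mean that AE recording ends at day 60, and a site that works from the text would carry on. With seven centers in four countries, practice could differ.

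Tolerability and safety are a stated secondary objective, and the article also lists AE incidence and severity under its primary endpoints heading. The late events that the Discussion describes are the kind most exposed to a schedule that stops at day 60. An AE incidence rate is also hard to interpret if some patients contribute about two months of recording and others a year.

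**Working it through.** The article states no figure on this point that could be reproduced, so the check consists of reading the table and counting visits and days.

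**Inputs**
- Scheduled post-baseline visits (Table 3): days 7, 15, 28 and 60; months 4, 6, 8 and 12.
- Last scheduled visit with an AE mark (Table 3): day 60 ± 7.
- Length of follow-up (Study organization): 12 months from randomization, taken here as day 365.
- Onset of neurological events and arthritis (Discussion): after day 40.
- Sample size and allocation: 240 patients, 1:1:1, so 240 / 3 = 80 per arm.

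**1. Is the blank a reading error?** The PCR row of the same table is blank at the side effect visit and marked at months 4 to 8 and at month 12, as expected for an efficacy measure. The AE row is marked at the side effect visit and blank at those later visits. Both rows fit the nine column headings, so the columns are aligned and the blank appears to be in the table itself.

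**2. Visits without an AE item.** Months 4, 6, 8 and 12 are 4 of 8 scheduled post-baseline visits.

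**3. Time without a scheduled AE item.** (365 − 60) / 365 = 305 / 365 = 84%. With the visit window the share runs from (365 − 67) / 365 = 82% to (365 − 53) / 365 = 85%.

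**4. Overlap with the late events.** Scheduled AE collection covers 60 − 40 = 20 days of the period after day 40 (13 to 27 days with the ±7-day window).

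**5. Consequence for the incidence rates.** If the rate is per unit of time, the two rules give very different denominators. With full follow-up of 80 patients per arm, they are 80 × 60 = 4,800 patient-days or 80 × 365 = 29,200 patient-days, a ratio of 365 / 60 = 6.1. If the rate is a proportion of patients, the denominator stays the same but the period at risk differs by the same factor. In either case the reader needs to know which period applies.

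**6. Side by side.** The text includes the follow-up period in AE reporting. The schedule for that period has no AE item. The text on spontaneous consultation does not fill the gap, because it refers to the treatment phase.

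**The case against.** The strongest reply is that the text already settles the matter. It obliges reporting in follow-up, and directed history-taking and physical examination at months 4, 6, 8 and 12 give each site the opportunity to learn of an event. The side effect visit carries an AE mark with no day limit in the table. The article also condenses a full protocol that is not shown. Much of this stands. It rules out the inference, which a reader might draw, that late toxicity is missed. What remains is a risk of incomplete or uneven recording where a site follows the table. The contradiction lies between two statements in the article itself, so it is not a detail merely left to a fuller document.

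A reader might also infer that the safety comparison favours the 60-day regimens. Measured from the last active dose, scheduled AE collection lasts 60 − 15 = 45 days in the 15-day arm (38 to 52 with the window) and 60 − 60 = 0 days (at most 7) in the 60-day arms. The documents do not support that conclusion:
- From randomization, scheduled AE collection ends at the same visit, day 60 ± 7, in every arm. That is a sound basis for a randomized comparison.
- The documents give no rate of AEs that begin after day 60, so neither the existence nor the size of a bias can be shown.
- The day counts assume that dosing is completed as planned. The Introduction reports that around 15% of patients with AEs stop treatment for good, and early stoppers have AE visits after their last dose.

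Nor is a comparison over an equal period after the last active dose the answer. A 45-day post-dose period would mean 15 + 45 = 60 days of total observation in the 15-day arm and 60 + 45 = 105 days in the others, which gives the longer regimens more time to accrue events.

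Finally, AEs that lead to discontinuation, the safety component of the sample-size hypothesis, occur during treatment and so fall within the marked visits.

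**Conclusion.** The point holds as an inconsistency between text and table that should be reconciled. If Table 3 is followed, about 305 of 365 days (82% to 85% with the visit window) and 4 of 8 post-baseline visits have no scheduled AE item. Events after day 60, including the late neurological events and arthritis that the Discussion relates to cumulative dose, may then be recorded incompletely or differently across centers. The period to which the AE incidence rates refer is ambiguous, at about 60 days or 12 months.

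The 84% measures time without a scheduled item, not events lost, and most of it is time off drug. Onset or persistence of the late events beyond day 60 is plausible from the article's account of their timing, but the article does not state it. The figures take month 12 as day 365. The point does not affect the efficacy endpoint or the sample size.

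**What to change.** Reconcile the two places by marking AEs at the month 4, 6, 8 and 12 visits in Table 3, in line with the reporting rule in the text. State the observation period for the AE incidence rates, and report AE incidence per arm from randomization over 12 months alongside the 60-day treatment phase. Both periods start at randomization and are planned to be the same length in every arm.

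The visits, history-taking and examination already take place, so the cost is a little extra data entry and a second summary table. For patients who have already passed these visits, AEs noted in the history or examination could be carried over from the source records, with a statement of how far this was possible at each center.

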#### Primary endpoints

The primary endpoint is parasitologic response, defined as maintained negative qualitative PCR results during the 12-month follow-up period. For efficacy assessments, the end of treatment of each treatment arm will be defined in accordance with the duration of the treatment regimen. Incidence and severity of AEs and those leading to treatment discontinuation will also be recorded.

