### Sample size and data analysis

For the sample size calculation, we considered a superiority design for two-sample comparison of proportions. We hypothesize a reduction of 50% of the total number of patients who either have a positive PCR result during follow-up or have to discontinue the treatment due to AEs, has been taken into account as a hypothesis. It is estimated that in the standard arm of treatment, 40% of patients will be evaluated as treatment failures according to the intention-to-treat principle.

Given the expected proportions in every group and given that we plan two pairwise comparisons for a power of 80% and a type I error of 0.05, the total number of patients that should be included in the study is 240, which will comprise 60 participants per country.

The categorical data will be presented as absolute numbers and proportions, and the continuous variables will be expressed as means and standard deviations when normal distribution is demonstrated (using the Kolmogorov-Smirnov test) or as medians and interquartile ranges when it is not.

For comparison of the distribution of categorical variables, the χ^2^ test or Fisher’s exact test will be used, and the Mann-Whitney *U* test or Student’s *t* test will be used for continuous variables, respectively, depending on the presence or not of normal distribution.

A comparative analysis of the main clinicoepidemiological variable among the three groups will be carried out. The primary efficacy analysis will be the comparison of the proportion of patients with sustained parasitologic clearance of each treatment arm compared with the standard arm of treatment. The time until the first positive PCR result for *T. cruzi* will be evaluated by Kaplan-Meier survival analysis with the log-rank test for significance.

The proportion of patients with SAEs and/or AEs leading to treatment discontinuation will be described per trial arm and by System Organ Class (using preferred terms defined by MedDRA 13.1), according to the National Cancer Institute’s Common Terminology Criteria for Adverse Events (version 4.03). Incidence rate and 95% confidence interval will be presented per trial arm for SAEs and AEs per category, along with the most frequent AEs.

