Safety laboratory parameters (hematology and biochemistry) will also be described individually per trial arm, showing the proportion of patients by degree of elevation relative to upper limit of normal and baseline values, as well as blood level changes over time.

Safety data will be correlated to efficacy and treatment compliance data and to PK parameters. Differences in the rate of absorption in serology will be estimated with *t* test pairs or the Wilcoxon test, depending on their distribution. All safety analyses will be carried out on all patients treated, understood as all patients who receive at least one dose of treatment. Finally, the sensitivity, specificity, and positive and negative predictive values of the presence of HLA-B*3505 and their relationship with the occurrence of SAEs will be calculated.

The efficacy analysis will be carried out according to the intention-to-treat principle. The group of patients analyzed will be all randomized patients in each of the treatment branches. Cases lost during follow-up and dropouts will be considered treatment failures.In addition, a per-protocol analysis will be defined as all patients receiving randomized treatment who meet the main criteria, have not permanently left the administration of the treatment, and have no other protocol deviation. Patients lost to follow-up will be excluded unless they present a positive PCR result, in which case, they will be included in the analysis. The results will be analyzed using IBM SPSS Statistics version 19.0 software (IBM Corp., Armonk, NY, USA).

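### The protocol gives two different answers on whether a patient who stops benznidazole early stays in PCR follow-up, and an early exit is scored as a parasitological failure

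*Protocol article*

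**What the plan says.** Four places in the protocol article bear on this.

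- **Study organization, follow-up phase.** One trigger for follow-up is "when a severe AE that obliges the patient to suspend the medication occurs". Completing the scheme and the patient's own decision to stop are the others. After any of them, "this phase will begin, and it will last up to 12 months after randomization". Table 3 schedules PCR at months 4, 6, 8 and 12.
- **SAEs and unblinding: care of patients with AEs.** "The study may be interrupted in case of voluntary decision of the patient at any time if an AE forces interruption of the treatment". The sentence goes on: "if significant protocol violations occur, or if the treating physician deems it would benefit the patient (intention-to-treat principle"). The sentence before it describes patients who complete treatment and follow-up and attaches a per-protocol label to them.
- **Primary endpoints.** "The primary endpoint is parasitologic response, defined as maintained negative qualitative PCR results during the 12-month follow-up period". The analysis section agrees: "The primary efficacy analysis will be the comparison of the proportion of patients with sustained parasitologic clearance" in each arm against standard.
- **Sample size and data analysis.** Efficacy is analysed by intention to treat in all randomized patients, and "Cases lost during follow-up and dropouts will be considered treatment failures". The sample size hypothesis in the same section uses a wider failure definition: a positive PCR or discontinuation because of AEs, at 40% in the standard arm and halved in an experimental arm.

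**The concern.** An AE that ends treatment leads to continued PCR visits under one section and permits exit from the study under the other. Centres in four countries could apply this differently.

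The consequence runs through the missing-data rule. A PCR-negative patient who leaves under the AE section is a dropout and is scored as not having sustained clearance, although visits to measure it were already scheduled. If AE stops differ between regimens, a difference in tolerability then appears as a difference in parasitological response. A superiority claim could arise, or be inflated, without any difference in PCR.

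The per-protocol analysis does not repair this, because it leaves out patients who permanently stopped treatment. The lost results also bear on the trial's own rationale: the section on shorter regimens reports notable cure among patients who abandoned treatment, and the Discussion uses this to justify the short arm.

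**Working it through.** **1. The planned size.** Inputs from the sample size section: 40% against 20% failure, power 80%, alpha 0.05 (two-sided assumed). With pooled variance, n = [1.96·√(2·0.30·0.70) + 0.842·√(0.24 + 0.16)]² / 0.20² = 81.2, so 82 per arm and 246 in total. With unpooled variance, n = (1.96 + 0.842)²·0.40 / 0.04 = 78.5, so 79 per arm and 237 in total. The stated 240 (80 per arm) is reproduced, with power of 79.4%. The plan was therefore sized on the composite failure definition, with no addition for dropout.

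**2. The rules side by side.**

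| Event | Follow-up phase | AE section |
|---|---|---|
| AE forces treatment to stop | follow-up to month 12 (severe AE) | study may be interrupted |
| Patient decides to stop drug | follow-up to month 12 | patient's decision may end the study |
| Protocol violation | not addressed | study may be interrupted |
| Physician judgement | not addressed | study may be interrupted |

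The direct conflict is in the first row. The second is a conflict only if stopping drug is treated as leaving the study. In the last two rows there is no contradiction with the follow-up text. The difficulty there is that outcome collection may end for patients whom the intention-to-treat analysis must still score.

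**3. Effect on the scored endpoint.** Let d be the proportion stopping for AEs, f the PCR failure risk (the same in stoppers and non-stoppers, and in every arm), and L the share of stoppers who leave before their PCR outcome is known. Scored failure is F = f + d·L·(1 − f), so the gap between arms is (d₀ − d₁)·L·(1 − f).

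The Introduction gives about 15% definitive stops. The 5% for an experimental arm, f = 25% and L = 1 are assumptions.

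- Standard arm: 0.15 + 0.85·0.25 = 36.3%. At 80 per arm, 0.15·80 = 12 patients are stoppers.
- Experimental arm: 0.05 + 0.95·0.25 = 28.8%.
- Gap: 7.5 points with no difference in PCR response.

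**4. Calibrated to the plan's 40%.** If 15% of the standard arm stop and all exit, f = 1 − 0.60/0.85 = 29.4%. With 5% stops, the experimental arm scores 0.05 + 0.95·0.294 = 32.9%, a gap of 7.1 points. The chance of declaring the experimental arm better at 80 per arm is Φ[(0.0706 − 1.96·0.0761)/0.0759] = 15%, against a nominal 2.5% in that direction.

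**5. Range.**

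| Stops, standard vs experimental | f | L | Gap (points) | Chance of declaring experimental better |
|---|---|---|---|---|
| 30% vs 5% | 29.4% | 1 | 17.7 | 62% |
| 15% vs 0% | 29.4% | 1 | 10.6 | 29% |
| 15% vs 5% | 29.4% | 1 | 7.1 | 15% |
| 15% vs 5% | 29.4% | 0.5 | 3.5 | 7% |
| 6% vs 5% | 25% | 1 | 0.75 | not computed |
| any | any | 0 | 0 | 2.5% |

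The 6% row reflects an ambiguity in the Introduction. If its 15% refers to patients with AEs (40% to 98% of those treated), stops among all treated are 0.15·0.40 = 6% to 0.15·0.98 = 14.7%.

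**The case against.** Several counter-arguments have force.

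- **The AE section is permissive.** It says the study may be interrupted. Without a comma after the reference to the patient's decision, it can also be read as covering only a patient who chooses to leave after an AE, which is ordinary withdrawal. This limits the size of the problem but does not remove the ambiguity, and the violation and physician clauses remain.
- **The intention-to-treat label may only name an analysis set:** completers count per protocol, and interrupted patients still count by intention to treat. That reading is plausible and fits the analysis section, so the label alone proves little.
- **Not every stopper is scored as a failure.** A reader might infer that, but the imputation covers lost cases and dropouts. A patient off drug who attends the PCR visits is not clearly either.
- **The sample size section already counts AE discontinuation as failure.** This is the strongest objection. A reader might infer that the AE section alone brings tolerability into the endpoint, and that rewording it would cure the problem. The documents do not support that: under the sample size definition the mixing would remain with complete PCR follow-up. It follows that the endpoint and sample size sections must be reconciled as well.
- **Different AE rates are not established.** The protocol cites no link between drug concentration and AEs and no higher AE frequency at 400 mg/day, and it places skin and digestive events around day 10, within the 15-day regimen. It also places neurological events and arthritis after day 40 and ties them to cumulative dose, so a difference is plausible but unproven.

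**Conclusion.** The inconsistency is real and should be fixed. For an AE-forced stop, one section continues PCR follow-up and another permits exit. The resulting dropouts are scored as failures on an endpoint that the objectives and endpoint sections define by PCR alone.

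The figures are illustrations and do not estimate bias in this trial. The 7.5-point gap (7.1 when calibrated to 40%) needs every stopper to leave, equal PCR risk in stoppers and non-stoppers, 15% stops in the standard arm and an unsourced 5% in the other. It falls to 0.75 points at 6% against 5%, and to zero if stoppers stay in follow-up and are scored on PCR. The direction favours whichever arm is better tolerated, and the documents do not establish which that will be.

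A reader might conclude that the trial's primary result is bound to be biased. The text does not support that, since the follow-up section already provides for keeping these patients.

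**What to change.** 1. **Reconcile the follow-up phase with the AE section.** State that stopping study drug, for whatever reason the protocol allows, does not by itself end outcome collection, and that PCR visits to month 12 continue unless the patient withdraws consent or is truly lost. The rules on when treatment is stopped are outside this point and stay as they are.
2. **In the same edit, reconcile the primary endpoint, sample size and intention-to-treat text** on whether AE discontinuation is part of the primary failure definition.
3. **Report the observed PCR results of discontinuers,** at least as a sensitivity analysis, so that parasitological response and tolerability can be separated under either definition.

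Steps 1 and 3 cost a wording change, a reminder to sites and one extra analysis. The visits are already scheduled. Results not collected cannot be recovered later, so step 1 is urgent while patients are in follow-up.

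Step 2 may cost more. If the primary analysis becomes PCR alone and the standard-arm rate falls below 40%, the basis of 240 changes. For example, with an assumed 25% and the planned halving to 12.5%, power at 80 per arm is about 53%, and about 152 per arm would be needed for 80% (two-sided 0.05, pooled formula as above). Keeping the composite preserves the sizing, but the endpoint must then be described as a composite and not as parasitological response.
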